# Dietary approaches to treat MS-related fatigue: comparing the modified Paleolithic (Wahls Elimination) and low saturated fat (Swank) diets on perceived fatigue in persons with relapsing-remitting multiple sclerosis: study protocol for a randomized controlled trial

**DOI:** 10.1186/s13063-018-2680-x

**Published:** 2018-06-04

**Keywords:** Multiple sclerosis, Fatigue, Diet, Accelerometer, Quality of life, Intervention, Swank diet, Wahls elimination diet

## Abstract

**Background:**

Fatigue is one of the most disabling symptoms of multiple sclerosis (MS) and contributes to diminishing quality of life. Although currently available interventions have had limited success in relieving MS-related fatigue, clinically significant reductions in perceived fatigue severity have been reported in a multimodal intervention pilot study that included a Paleolithic diet in addition to stress reduction, exercise, and electrical muscle stimulation. An optimal dietary approach to reducing MS-related fatigue has not been identified. To establish the specific effects of diet on MS symptoms, this study focuses on diet only instead of the previously tested multimodal intervention by comparing the effectiveness of two dietary patterns for the treatment of MS-related fatigue. The purpose of this study is to determine the impact of a modified Paleolithic and low saturated fat diet on perceived fatigue (primary outcome), cognitive and motor symptoms, and quality of life in persons with relapsing-remitting multiple sclerosis (RRMS).

**Methods/design:**

This 36-week randomized clinical trial consists of three 12-week periods during which assessments of perceived fatigue, quality of life, motor and cognitive function, physical activity and sleep, diet quality, and social support for eating will be collected. The three 12-week periods will consist of the following:*Observation*: Participants continue eating their usual diet.*Intervention*: Participants will be randomized to a modified Paleolithic or low saturated fat diet for the intervention period. Participants will receive support from a registered dietitian (RD) through in-person coaching, telephone calls, and emails.*Follow-up*: Participants will continue the study diet for an additional 12 weeks with minimal RD support to assess the ability of the participants to sustain the study diet on their own.

**Discussion:**

Because fatigue is one of the most common and disabling symptoms of MS, effective management and reduction of MS-related fatigue has the potential to increase quality of life in this population. The results of this study will add to the evidence base for providing dietary recommendations to treat MS-related fatigue and other symptoms associated with this disease.

**Trial registration:**

ClinicalTrials.gov, NCT02914964. Registered on 24 August 2016.

**Electronic supplementary material:**

The online version of this article (10.1186/s13063-018-2680-x) contains supplementary material, which is available to authorized users.

## Background

Fatigue is one of the most common and disabling symptoms of multiple sclerosis (MS), diminishing quality of life (QOL) and contributing to early exit from the workforce [1, 2]. MS-related fatigue is most commonly managed through multiple interventions, including disease-modifying drugs and stimulants, exercise, energy conservation, and stress management techniques [3]. Although exercise augmented by electrical muscle stimulation can be modestly effective in reducing perceived fatigue [4, 5], studies investigating the efficacy of pharmaceutical therapies have shown conflicting results [6–8]. Because drug treatment has not been effective, dietary interventions are being explored. Statistically and clinically significant reductions in perceived fatigue severity in persons with progressive multiple sclerosis (pwPMS) have been reported with use of a multimodal intervention consisting of a modified Paleolithic diet, stress reduction, exercise, and electrical muscle stimulation [4, 5].

Interventions considering the whole diet (vs. supplement-based, single-nutrient focus) have been used in treating or preventing diseases, including psoriasis [9], cancer [10, 11], and neurological diseases [12]. Emerging data support the notion that environmental rather than genetic factors are likely the predominant causes of MS [13]. Given that food consumed is a major component of the environment, it is conceivable that improving the quality of the diet may have a significant impact on the development of MS. The relationship between the quality of the diet and MS-related symptoms such as fatigue is unknown. In this study, we will compare two dietary patterns for the treatment of MS-related fatigue: the modified Paleolithic diet (Wahls elimination diet) and a low saturated fat diet (Swank diet).

One early dietary intervention for individuals with MS was based on the observation that high levels of saturated fat in the diet were associated with increased risk for MS in Norway [14, 15]. [name] theorized that a diet high in saturated fats causes more rapid disease progression. [name] followed 144 patients with mild to more severe disability for 34 years. These individuals had agreed to consume a diet containing < 20 g of saturated fat per day and report their dietary adherence. The patients’ clinical outcomes were monitored, including physical and mental performance [16–21]. The Swank study found that the number of relapses and progression of disability was associated strongly with dietary saturated fat consumption [17–22]. The 50-year follow-up is a strength of the Swank study, but the absence of a control group and lack of brain imaging are limitations.

Consumption of vegetables has also been associated with favorable health outcomes related to MS. Notably, the mean daily serving of vegetables is associated with lower risk of developing obesity [23], which is a risk factor for and a common comorbid diagnosis of those with MS. Increased consumption of vegetables is associated with lower Expanded Disability Status Scale scores [24], insulin sensitivity, blood pressure, body weight, and body mass index (BMI). Considering these observations, researchers in a more recent randomized controlled trial used a vegetarian version of the Swank diet [25], also known as the McDougall diet. Measures included the Fatigue Severity Scale (FSS), 36-item Short Form Health Survey (SF-36) quality-of-life scores, lipids, weight, BMI, and brain magnetic resonance imaging (MRI) scans at baseline and at 1 year [26]. Favorable reductions in weight, BMI, and total cholesterol were observed, but no statistically significant differences in MRI findings or SF-36 quality-of-life scores were reported [26].

Another diet of interest to the MS community is a Paleolithic diet [27]. [name] recommendations for a modern version of the Paleolithic diet stresses the consumption of meats, vegetables, and fruits; excludes grains, legumes, and dairy [27, 28]; and excludes nightshade vegetables (potatoes, tomatoes, peppers, and eggplants) [29] for persons with rheumatoid arthritis. Recently tested for its impact on various biomarkers in healthy individuals, the Paleolithic diet was associated with improvements in blood pressure, BMI [30], total cholesterol, insulin sensitivity, fasting insulin, and arterial distensibility [31]. In a study of patients with type 2 diabetes, the Paleolithic diet was shown to be more satiating per calorie than the American Diabetes Association (ADA) diet, which encourages increased intake of vegetables, dietary fiber, whole-grain bread and cereal products, fruits, and berries and decreased intake of total fat with more unsaturated fat [32]. In a crossover study comparing the Paleolithic diet with the ADA diet, the Paleolithic diet was superior to the ADA diet with respect to improving blood pressure, lipid profile, and glycemic control [33]. Finally, in a randomized controlled study of obese persons with metabolic syndrome, comparison of the Paleolithic diet with the control diet, which was an isoenergetic diet based on Dutch dietary guidelines, the Paleolithic diet was associated with greater improvements in blood pressure, fasting levels of lipids, and weight loss than the control diet [34].

A modified version of the Paleolithic diet was shown to reduce perceived fatigue in pwPMS (either secondary or primary progressive multiple sclerosis [SPMS or PPMS, respectively]) [4, 5] as part of a multimodal intervention (modified Paleolithic diet, targeted vitamin supplementation, stress-reducing practices, exercise, and electrical muscle stimulation). The study diet stressed the consumption of more vegetables, with a target of 6 to 9 cups of vegetables and fruit per day, and recommended somewhat less meat than Paleolithic diets tested in the previously mentioned studies. At enrollment, study participants were consuming less than 1.5 servings of vegetables per day but raised this to an average of 8 servings per day by month 12 [5]. The dietary component of the multimodal intervention was significantly associated with favorable changes in mood and cognition between baseline and 12 months, whereas the nondietary components were not [25]. It is unknown whether the dietary component of the multimodal intervention also significantly contributed to the observed reduction in perceived fatigue [4, 5]; however, several participants anecdotally reported that deviations from the study diet resulted in a sharp worsening of their fatigue and noted that the fatigue resolved with stricter adherence to the study diet. Data from another pilot randomized controlled trial also showed significant reductions in perceived fatigue (as assessed by FSS) in individuals with relapsing-remitting multiple sclerosis (RRMS) following a modified Paleolithic diet intervention [35].

To establish the specific effects of diet on MS symptoms such as fatigue, this study focuses on diet only instead of the previously tested multimodal intervention. The modified Paleolithic diet continues to stress a high intake of vegetables but also eliminates foods to which some individuals may be sensitive: eggs and nightshade vegetables [29]. To enhance adherence and reduce the rate of dropout, which occurred early in the intervention among participants in a nondiet control group [35], control participants will be assigned a second diet, a low saturated fat (Swank) diet, which is also popular among the MS community and has research to support its efficacy.

## Methods/design

### Aims of study

In this study, we will compare the impact of the modified Paleolithic diet (Wahls elimination diet) and a low saturated fat diet (Swank diet) on perceived fatigue, cognitive and motor symptoms, and quality of life in persons with RRMS, a milder form of disease that often transitions to a more progressive and severe form of MS. We hypothesize that participants following the modified Paleolithic diet will have a clinically greater reduction in FSS score than participants following the low saturated fat diet.

#### Research hypothesis 1a

After 12 weeks of the diet intervention, relative to the observation period, at least 15% of participants in the low saturated fat diet group will demonstrate decreased perceived fatigue (assessed by FSS score), 30% will have improvement in QOL mental health and physical health scores (mean score increase of > 5 points), 50% will demonstrate improved cognition (> 5% improvement in mean Symbol Digit Modalities Test–Oral [SDMT-O] score), and 30% will demonstrate improved motor function (> 5% improvement in mean distance of 6 Minute Walk Test [6MWT]). In the modified Paleolithic diet group, ≥ 60% of the participants will demonstrate decreased perceived fatigue, 70% will have improvement in QOL mental health and physical health score, 70% will demonstrate improved cognition, and 55% will demonstrate improved motor function.

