#### Research hypothesis 1b

After 12 weeks of the diet intervention, participants in the low saturated fat diet group will not have clinically or statistically significant reductions in fatigue or improvements in QOL measures or motor and cognitive function relative to the observation period, whereas participants in the modified Paleolithic diet group will have clinically and statistically significantly reduced fatigue and improved QOL measures and motor and cognitive function as measured by changes in mean scores of the aforementioned measures.

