#### Research hypothesis 2c

By 12 weeks after the initiation of diet, participants in the modified Paleolithic diet group will have clinically greater improvement, relative to the observation period, with respect to quality of life (assessed by Multiple Sclerosis Quality of Life 54 [MSQOL54] instrument) and mood (assessed by Hospital Anxiety and Depression Scale [HADS]) than those in the low saturated fat diet group.

#### Research hypothesis 3

After 24 weeks of the diet intervention, changes in the measures identified in hypotheses 1a and 1b observed at 12 weeks will be sustained in ≥ 80% of the participants in both diet groups.

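### Hypothesis 1a sets no size cut-off for an FSS response, so its 15% low saturated fat target is met with no effect at all, and hypothesis 3 leaves the denominator of its 80% open

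*Protocol article*

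**What the plan says.** Research hypothesis 1a of the protocol article sets responder percentages for each arm after 12 weeks of diet, relative to the observation period. For the primary outcome in the low saturated fat arm: "at least 15% of participants in the low saturated fat diet group will demonstrate decreased perceived fatigue (assessed by FSS score"). The other three measures carry a size cut-off. For SDMT-O and for 6MWT distance it is a gain above 5%, with targets of 50% and 30% in this arm. The quality-of-life target reads: "30% will have improvement in QOL mental health and physical health scores (mean score increase of > 5 points"). For the modified Paleolithic arm: "≥ 60% of the participants will demonstrate decreased perceived fatigue, 70% will have improvement in QOL mental health and physical health score", with 70% for cognition and 55% for motor function.

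Research hypothesis 1b expects that "participants in the low saturated fat diet group will not have clinically or statistically significant reductions in fatigue" relative to the observation period. Research hypothesis 3 then states, for the end of 24 weeks on diet, that "changes in the measures identified in hypotheses 1a and 1b observed at 12 weeks will be sustained in ≥ 80% of the participants". It applies this to each of the two arms.

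Table 4 (Power and sample size justification) works with mean differences and 34 per group. Its FSS row gives a within-group difference of 1.2–2.0, SD 1.1–1.4 and correlation 0.6, and a between-group difference of 0.7.

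**The concern.** A fatigue score varies between visits without any treatment. If every decrease counts as a response, close to half of an untreated group responds. A 15% target then sits so far below the no-effect rate that meeting it says nothing about the diet. The 60% target is above the no-effect rate, but a shift too small to matter by Table 4's own figures can reach it.

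Hypothesis 3 raises a related problem. Sustaining a change presupposes that a change occurred, and the article does not say whether people without one are counted. If the denominator is chosen after the data are seen, the same data could pass or fail.

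**Working it through.** **Inputs.** The percentages come from hypothesis 1a; the SDs, correlations and n = 34 from Table 4. Assumptions: the SD column is the SD at one visit, changes are normal, and the FSS score is the mean of its nine items, so it moves in steps of 1/9.

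**1. Table 4 first.** SD of change = SD × √(2(1 − r)).
- FSS: 1.1 × √0.8 = 0.984; 1.4 × √0.8 = 1.252
- Physical composite: 16 × √0.8 = 14.3; mental composite: 17 × √1.0 = 17.0
- 6MWT: 50 × √1.0 = 50

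Paired power at two-sided 0.05 is above 0.999 for FSS (difference 1.2), 0.997 and 0.984 for the two composites, and 0.983 for 6MWT. These agree with the stated floors of 0.85 and 0.90. The percentages in 1a have no calculation of their own to reproduce.

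**2. FSS, low saturated fat, no effect.** The share with any decrease is Φ(−(1/18)/SD of change), which is 0.477 for 0.984 and 0.482 for 1.252. The target needs 0.15 × 34 = 5.1, so 6 or more of 34.

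| Decrease counted as a response | No-effect share | Chance of 6 or more of 34 |
|---|---|---|
| any | 47.7–48.2% | > 0.999 |
| 0.7 or more | 23.8–28.8% | 0.85–0.95 |
| 1.2 or more | 11.1–16.9% | 0.17–0.52 |

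Turned round, 15% is the expected share with any decrease only if mean FSS worsens by 1.036 × 0.984 − 0.056 = 0.96 to 1.036 × 1.252 − 0.056 = 1.24 points.

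**3. FSS, modified Paleolithic.** The target needs 0.60 × 34 = 20.4, so 21 or more. With no effect the chance is 0.07–0.08. With a mean fall m the share is Φ((m − 1/18)/SD of change):
- m = 0.30: share 0.58–0.60, chance of meeting the target 0.38–0.48
- m = 0.35: share 0.59–0.62, chance 0.46–0.58

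**4. Quality of life, low saturated fat.** No-effect shares are 1 − Φ(5/14.3) = 0.363 (physical) and 1 − Φ(5/17) = 0.384 (mental), both above the 30% target. The chance of 11 or more of 34 is 0.74 and 0.82. If both composites must improve, the no-effect share is 18–25% for an assumed correlation of 0.3–0.7 between the two changes, and reaches 30% only near 0.9.

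**5. Walking, low saturated fat.** The share is 1 − Φ(0.05M/50), where M is a baseline mean that the article does not give. For assumed M of 300, 400, 500 and 600 (in the unit of the SD) it is 38%, 34%, 31% and 27%. It falls below 30% above M = 0.5244 × 50/0.05 = 524.

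**6. Other modified Paleolithic targets, no effect.** Quality of life (24 or more of 34, each composite): below 0.001. 6MWT (19 or more of 34): at most 0.03 for M of 300 or more.

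**7. Hypothesis 3 beside 1a and 1b.** Taken over all participants, 80% exceeds every percentage in 1a, the highest being 70%. In the low saturated fat arm 1a gives 15–50%, and 1b expects no significant mean change. Taken over those who had changed, there is no conflict, but 15% of 34 is about 5 people.

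**The case against.** The strongest reply is that the 1a percentages are expectations. No success rule is attached to them, and the FSS figures are floors. Hypotheses 2a–2c compare the diets directly, Data analysis specifies mixed models, and a working responder definition may sit in a fuller document. Most of this stands, and it confines the point to hypotheses 1a and 3. It does not rescue the 15%: that figure is stated, and neither a 0.7 nor a 1.2 cut-off makes it a demanding target.

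A reader might infer several stronger things that the article does not support:
- **That inert diets would confirm 1a.** They usually would not. The modified Paleolithic targets would mostly fail (steps 3 and 6). The low saturated fat cognition target of 50% would tend to fail as well, since under symmetric zero change fewer than half can pass a positive cut-off.
- **That chance alone meets the quality-of-life and walking targets.** The first holds only if each composite is scored separately, and the wording can be read as requiring both. The second depends on the missing baseline mean. If visits 1 and 2 are averaged as the reference (same SD and correlation throughout), the SD of change is 50 × √0.75 = 43.3 and the crossing point drops to 0.5244 × 43.3/0.05 = 454.
- **That hypothesis 3 contradicts 1a.** The text does not say all participants. Only someone who changed can sustain a change, so the defect is ambiguity. Nor does 1a expect most people not to change in the modified Paleolithic arm, where its figures are 55–70%.

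**Conclusion.** The point holds for the FSS targets in hypothesis 1a and for the denominator in hypothesis 3. The 15% figure carries no information: its no-effect rate is about 48%, which hardly depends on the SD because it follows from symmetry around zero change. The 60% figure can be met with a mean fall of about half of Table 4's 0.7 or less. The rates at the 0.7 and 1.2 cut-offs do rest on Table 4's SDs and correlation and on a single-visit reference; averaging the reference would lower them. The quality-of-life point is conditional on separate scoring, and the walking point on a baseline mean not given. The randomized test of the diets in hypotheses 2a–2c is not affected, so this should be corrected but does not threaten the main comparison.

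**What to change.** - Pre-specify the fall in FSS that counts as a response, with a rationale. Table 4's 0.7 and 1.2 are differences in group means, so neither is automatically an individual cut-off; show results at both.
- Judge 1a by the between-diet difference in responder proportion with a 95% CI, and drop the fixed within-arm percentages. Adding a cut-off while keeping the 15% is not enough, as the table shows.
- Report the responder rate from visit 1 to visit 2, when no study diet was given, beside the diet results.
- State whether one or both quality-of-life composites must improve.
- For hypothesis 3, report the proportion sustained among week-24 responders, together with the week 24 to 36 mean change by arm with CIs.

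The cost is rewording two hypotheses and a few extra summaries of data already being collected. The drawback is that responder proportions have less power than means, so they should remain supportive of hypothesis 2a. The sustained proportion may also rest on few people in an arm with few responders.

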#### Research hypothesis 1b

After 12 weeks of the diet intervention, participants in the low saturated fat diet group will not have clinically or statistically significant reductions in fatigue or improvements in QOL measures or motor and cognitive function relative to the observation period, whereas participants in the modified Paleolithic diet group will have clinically and statistically significantly reduced fatigue and improved QOL measures and motor and cognitive function as measured by changes in mean scores of the aforementioned measures.

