#### Dietary supplements

All study participants will follow the supplement regimen outlined in Table 1, with the exception of vitamin D_3_ (amount prescribed will vary on the basis of vitamin D level measured in the blood at visit 1 and subsequent visits as outlined in Table 2; target range, 40–80 ng/ml). After review of participant’s dietary supplement intake, study staff will ask participants to discontinue over-the-counter dietary supplements containing the study supplement ingredients (fish oil, vitamin D, vitamin B_12_, folate, and/or multivitamins) and use study supplements instead. Participants will be instructed to continue taking all other dietary supplements they have been using and not to begin any new supplements until after study completion. If the participant is asked to discontinue a supplement recommended by their physician or neurologist, the research team will send a letter to the treating physician, detailing which supplements have been discontinued and which supplements have been initiated as part of the study protocol.

**Table 2 Tab2:** Vitamin D dosing based on blood level

If vitamin D > 100 ng/ml and elevated calcium (Ca^2+^) > 10.2 mg/dl • Call study participant and have them stop vitamin D immediately, increase water intake. a. If Ca^2+^ level was 10.2–10.5: call your local physician, or urgent care for guidance. b. If Ca^2+^ level was 10.6 or higher: go to the emergency room for evaluation and probable intravenous fluids. • Stop or do not start taking the cod liver oil or the multivitamin • When vitamin D < 80 ng/ml, resume vitamin D at a reduced dose and cod liver oil and multivitamin per local primary care or neurology guidance • Call and notify the study participant’s primary care/neurology team about the high vitamin D level • Send letter to participant and primary care/neurologist	
If vitamin D > 100 ng/ml and normal calcium Ca^2+^ 8.5–10.2 mg/dl • Study staff will call the participant and have them stop all vitamin D supplements. Participant will follow up with their primary care doctor or neurologist. • Stop or do not start taking cod liver oil but may continue multivitamin • When vitamin D < 80 ng/ml, may resume vitamin D at a reduced dose and cod liver oil and multivitamin per local primary care or neurology guidance • Call and notify the study participant’s primary care/neurology team about the high vitamin D level • Send letter to participant and primary care/neurologist	

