### Power and sample size justification

Table 4 displays the mean minimum clinically important difference that can be detected for primary and secondary outcomes to be assessed in the study. The table also includes the SD and correlation between observations over time, with 34 patients in each group after attrition, and an alpha value of 0.05. The minimum differences and SDs are derived from the preliminary studies and peer-reviewed published MS longitudinal studies. Forty-five patients will be recruited in each group, assuming a 25% attrition rate, to attain the 34 patients needed in each group.

**Table 4 Tab4:** Power and sample size justification

Variable	Within Study Groups			Between Study Groups at Last Visit		
	MMCD	SD	Correlation	MMCD	SD Group A	SD Group B
Power is ≥0.85 for the primary outcome						
FSS-9	1.2–2.0	1.1–1.4	0.6	0.7 [35]	0.9	1.1
Power is ≥0.90 for secondary outcomes						
MSQOL-54						
PHC	11.5	16.0	0.6	17.0	17.0	19.0
MHC	12.0	17.0	0.5	18.0	18.0	19.0
6 min walk test	35	50.0	0.5	45.0	45.0	50.0
Timed 25 ft walk	2.9	4.0	0.5	4.0	4.0	4.3
9 hole peg test	5.5	8.0	0.5	8.0	8.1	8.3
PASAT^a^	4.2	6.0	0.5	5.8	6.0	6.3

*Abbreviations: FSS* Fatigue Severity Scale, *MSQOL-54* Multiple Sclerosis Quality of Life 54, *PHC* MSQOL-54 physical health composite score, *MHC* MSQOL-54 mentalhealth composite score, *PASAT* Paced Auditory Serial Addition Test, *MMCD* Minimun Mean Clinical Difference

^a^Power and sample size calculations based on PASAT. Per NMSS, SDMT-O replaces the PASAT measure in this study

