### Data analysis

All analyses will be completed by a masked statistician who will not have access to study diet assignment. Data analysis will include both intention-to-treat and per-protocol analytic methods. Data for this study will be analyzed using SAS® 9.4 software (SAS Institute, Cary, NC, USA). Statistical significance will be set at α ≤ 0.05. Descriptive statistics will be calculated for all variables at all data collection times. Outliers will be checked for accuracy and possible entry errors. Respondents who drop out of the study will be compared with those who complete the study so that differences in baseline characteristics that may affect the study results will be detected. Patterns of missing data (missing at random, not missing at random) will be investigated [61]. The analytic methods will account for the type of missing data. The distributions of continuous variables will be evaluated for normality and homogeneity of variance. Appropriate transformations will be applied as needed, and/or statistical analyses for nonnormal data will be performed. Collinearity among fixed effect variables will be examined.

Repeated-measures analyses will use generalized linear mixed models methods to test for within-group and between-group changes in both primary and secondary outcomes. Intraclass correlations for repeated measures within patients will be included in the model structure for analyses. Mixed models for both continuous and categorical outcomes will have both random and fixed effects. Fixed effects will include characteristics such age, sex, intervention group, time indicators, and group-by-time interactions. Intercepts and slopes may be considered as random effects.

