Both study groups are likely to experience reductions in MS-related symptoms. Differences within and between groups will be assessed for clinical significance, supported by statistical analyses. Because the primary outcome measure is a self-reported measure and not an objectively measured laboratory or imaging result, the NMSS requested two modifications in the study design. First, a 12-week observation period was added, during which participants continue to eat their usual diet, so that each participant can be her or his own control in the repeated-measures analyses. Second, an accelerometer measure was added to the study to provide an objective assessment of the change in physical activity, sleep duration, and sleep quality.

Given the anecdotal reports regarding improvement in MS symptoms with dietary changes, results from this study will contribute to understanding of the optimal dietary approach for reducing MS-related fatigue. Findings of the study as well as any challenges observed will be submitted to journals for publication. Published papers will be listed on the [name] website ([name]).

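### Hypothesis 1b sets a significant change on one diet against a non-significant change on the other; that pattern does not test the diet difference, and nothing ranks it below the direct comparison

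*Protocol article*

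**What the plan says.** Hypothesis 1b in the protocol article has two halves. For one arm, "participants in the low saturated fat diet group will not have clinically or statistically significant reductions in fatigue", and likewise no such gains in quality of life, motor function or cognition. For the other, "whereas participants in the modified Paleolithic diet group will have clinically and statistically significantly reduced fatigue", with gains in the same domains. Both are changes in mean scores relative to the observation period.

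The Data analysis section plans mixed models to "test for within-group and between-group changes in both primary and secondary outcomes", with group-by-time interactions among the fixed effects, and states that "Statistical significance will be set at α ≤ 0.05". The sample size section works "with 34 patients in each group after attrition" and "an alpha value of 0.05", without saying whether tests are one- or two-sided.

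Hypotheses 2a to 2c compare the diets directly but speak only of clinically greater improvement. Hypothesis 1b is the only one that names statistical significance. The Discussion expects that "Both study groups are likely to experience reductions in MS-related symptoms".

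**The concern.** Half of 1b is supported by a failure to reach significance. No equivalence margin or confidence bound accompanies it, so a true but modest benefit of the low saturated fat diet that is missed with 34 completers would count in favour of the prediction.

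The two halves together invite the conclusion that one diet works and the other does not. Two p-values falling on opposite sides of 0.05 do not establish that the arms differ. The Discussion's expectation that both groups improve describes the very setting in which the pattern misleads.

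A within-arm change also contains more than diet. Under Dietary supplements, "All study participants will follow the supplement regimen outlined in Table 1" (vitamin D dose apart), starting on day 11 of the diet, and dietitian counselling follows randomization in both arms. The observation period removes neither, because both begin after it. Only the randomized comparison balances them.

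At stake is a report that 1b was confirmed while the estimated difference between the diets is close to zero.

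**Working it through.** **Inputs.** From Table 4, FSS within groups: minimum clinical difference 1.2 to 2.0, SD 1.1 to 1.4, correlation 0.6. Between groups: difference 0.7, SDs 0.9 and 1.1. 34 analysed per arm, alpha 0.05. Assumed: two-sided tests, a simple paired analysis, equal SDs, independent arms, and Table 4's SD being that of a single measurement.

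**The plan's own figures.**
- Attrition: 45 × 0.75 = 33.75, in line with 34.
- Within-arm power: the SD of change is SD × √(2 × (1 − 0.6)), which is 0.984 at SD 1.1 and 1.252 at SD 1.4. For a 1.2-point change the paired t-test has power 0.9997 at SD 1.4 and about 1.000 at SD 1.1, so the stated power of at least 0.85 holds within arms.
- Between-arm power at 0.7 points: 0.81 for a plain two-sided t-test, 0.89 on change scores and 0.95 with baseline adjustment (the last two by normal approximation, with correlation 0.6). A workable direct test is therefore available.

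**Statistical significance alone, diets equally effective.** If each within-arm test has power p, the chance that the modified Paleolithic arm is significant and the other is not is p × (1 − p). Its maximum is 0.25, at p = 0.5. For FSS with n = 34:

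| Common true change | SD 1.1: p, p(1−p) | SD 1.25: p, p(1−p) | SD 1.4: p, p(1−p) |
|---|---|---|---|
| 0 | 0.025, 0.024 | 0.025, 0.024 | 0.025, 0.024 |
| 0.3 | 0.408, 0.241 | 0.330, 0.221 | 0.273, 0.199 |
| 0.4 | 0.634, 0.232 | 0.526, 0.249 | 0.440, 0.246 |
| 0.5 | 0.820, 0.147 | 0.716, 0.203 | 0.618, 0.236 |
| 0.7 | 0.981, 0.019 | 0.943, 0.054 | 0.886, 0.101 |
| 1.2 | 1.000, 0.000 | 1.000, 0.000 | 0.9997, 0.0003 |

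The maximum falls at a common change of 0.34 (SD 1.1) to 0.43 (SD 1.4). In simulation the direct between-diet test favoured the modified Paleolithic diet in about 2.5% of trials whatever the common change.

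**Other outcomes in 1b, same method.** At a common MSQOL-54 gain of 5 points (the cut-off in hypothesis 1a), Table 4's SDs and correlations give 0.25 for the physical composite and 0.24 for the mental composite. At half of Table 4's within-group difference, the 6-minute walk, timed 25-ft walk and peg test each give 0.25.

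**Adding the clinical condition (simulation, FSS, equal diets).** The modified Paleolithic arm must be significant and have an observed mean change at or above a threshold.
- Threshold 1.2, other arm misses both criteria: at most about 0.15% (common change 0.8, SD 1.4).
- Threshold 0.7 (Table 4's between-group value), other arm misses both: at most about 7% (common change 0.6, SD 1.4).
- Threshold 1.2, missing either criterion counts as failure: about 25% at a common change of 1.2.

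The protocol gives no FSS cut-off for 1b and does not say which reading applies.

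**The case against.** The strongest reply is that 1b is a research prediction and not a decision rule. The stated aim is a between-diet comparison, hypotheses 2a to 2c compare the arms directly, Table 4 sizes a between-group contrast, and the mixed model includes group-by-time terms. A reader might infer that 1b decides whether the diets differ, and hence that the trial carries a 25% false-positive rate. The documents do not support that: no section gives 1b this role, and the direct comparison keeps its nominal error.

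The 25% is also a maximum for one outcome on p-values alone. It needs within-arm power near 50% and is practically zero at a common FSS change of 1.2, the lower end of Table 4's within-group range. Hypothesis 1b asks for clinical as well as statistical significance. On the natural reading, where the low saturated fat arm shows neither, the FSS probability at the 1.2 threshold is about 0.15% or less. It also names several domains together, which can lower the chance that the whole pattern appears.

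Nor does the Discussion flatly contradict 1b. Some symptom reduction in both groups can coexist with a mean change that is neither clinically nor statistically significant in one of them. The same section says differences will be assessed for clinical significance, with statistics in support.

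All of this stands and limits the size of the problem. It leaves the form of 1b unchanged: support from non-significance, and a contrast of two verdicts. Because 2a to 2c speak only of clinically greater change, and no sentence subordinates 1b to them, a 1b success could still be reported beside a null between-diet result.

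**Conclusion.** The concern holds as a flaw in how 1b is framed. The pattern it predicts is neither a test of the diet difference nor evidence that the low saturated fat diet has no effect, and it sits badly with the expectation that both groups improve.

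Under equally effective diets, on statistical significance alone, the pattern in the stated direction has up to 25% probability per outcome, against 2.5% for the direct test. With the clinical criterion applied, the FSS maximum lies between about 0.15% and about 25%, according to the threshold and to how a miss is defined. These figures rest on the assumptions listed with the inputs; unequal SDs or dropout would shift the maximum somewhat. The planned between-diet comparison is unaffected; what is missing is a statement that it takes precedence.

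**What to change.** - Make 1b descriptive. Report within-arm changes as means with 95% confidence intervals, and say that they are not attributed to diet alone because supplements and dietitian counselling start with the diet.
- Remove the absence of significant change on the low saturated fat diet as something the trial can confirm.
- State in Data analysis that any claim that one diet does better rests only on the randomized between-diet (group-by-time) contrast, reported with its confidence interval.

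This means rewording one hypothesis and adding a sentence to the analysis section. It needs no new data or participants, and should be settled before diet assignment is unmasked. The price is that the trial makes no confirmatory within-arm claims.
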